### Statistical analysis

The data from all participating centers will be combined for statistical analysis of the primary and secondary outcomes as well as the AEs. The statistical analysis will be performed at the Institute of Basic Research in Clinical Medicine, China Academy of Chinese Medical Sciences. The primary outcome will be analyzed according to the intention-to-treat principle. To compare the difference between two groups, independent *t* tests (or the Mann–Whitney *U* test) will be used to analyze continuous data and the chi-squared or Fisher’s exact test will be used for categorical data. Repeated-measures ANOVA will be used to account for the time effect.

For all measures, two-sided *p* < 0.05 will be considered statistically significant. Statistical analyses will be performed using SAS software version 9.4 (SAS Institute, Cary, NC, USA).

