## Methods/design

### Study design and setting

This ongoing study was designed as a central-randomized, double-blind, parallel, placebo-controlled, multicenter trial. The study was designed using the Consolidated Standards of Reporting Trials (CONSORT) 2010 guidelines [10]. Also, we designed the trial based on the Standard Protocol Items: Recommendations for Interventional Trials (SPIRIT) statement. The study is being performed in three centers in China, namely: Dongzhimen Hospital, affiliated to Beijing University of Chinese Medicine; Beijing Tongzhou District Hospital of Traditional Chinese Medicine; and Beijing Pinggu Hospital of Traditional Chinese Medicine. Patients with cirrhotic ascites, who meet the inclusion criteria, will be allocated in a 1:1 ratio to either a LSXG group or a placebo group. Patients in the LSXG group will receive umbilical therapy with the LSXG cataplasm plus red light irradiation along with conventional treatment; patients in the placebo group will receive umbilical therapy with a placebo cataplasm plus red light irradiation along with conventional treatment. Based on clinical experience, the treatment will be administered once daily for up to 10 days, with a 30-day follow-up after the last treatment. The depth of ascites will be assessed as the primary outcome measurement. The abdominal perimeter, body weight, urine volume, the symptomatic score of TCM, and the Chronic Liver Disease Questionnaire (CLDQ) will be used as secondary outcome measurements. All assessments will be conducted at three time points: at baseline, after the last treatment, and after the 30-day follow-up period. The flow chart is shown in Fig. 1. We also provide the Standard Protocol Items: A Recommendations for Interventional Trials (SPIRIT) figure (Fig. 2) and the corresponding checklist (Additional file 1).

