### Primary outcomes

The primary outcome measurement will be the depth of ascites. It will be measured at baseline using B-ultrasound, after the intervention (10 days), and at the end of the 30-day follow-up period.

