## Discussion

Umbilical therapy with TCM formulations has a long history in China, and has been popularly used to treat various diseases, including cirrhotic ascites. Through being applied to the umbilical region, TCM may be absorbed into the blood quickly and stimulate peripheral nerves, which may be the reason for its action. Also, as a complementary therapy, it is easy to operate and convenient, compared with acupuncture, moxibustion, and TCM soups.

Previous studies preliminarily showed that umbilical therapy is effective and safe in treating cirrhotic ascites [8, 9, 16–19]. One meta-analysis demonstrated that umbilical therapy was more effective in increasing 24-h urinary volume, decreasing patients’ weight and abdominal circumference, compared with conventional medicines. Adverse reactions were rarely reported, which often include skin itching or partial flushing due to the adhesive plaster [8]. Another meta-analysis of mirabilite umbilical compress in treatment of ascites in liver cirrhosis showed similar results [9]. Application of Shehuang Paste to the umbilical area was also reported to reduce blood flow of the portal vein and the splenic vein, and to lower the content of endotoxin, nitric oxide, and endothelin-1 [8].

However, the lack of high-quality evidences limits the application of umbilical therapy [8]. Most studies were small sample, unblind, and based on one medical center, which may lead to bias caused by confounding factors. Besides, some studies took the 24-h urinary volume, patients’ weight, and abdominal circumference change as primary outcomes, which could not reflect the dynamic change of ascites directly [18, 20]. Based on previous research [14], our study will be the first central-randomized, double-blind, parallel, placebo-controlled, multicenter trial, using the dynamic change of ascites by B-ultrasound as the primary outcome. In conclusion, we present the protocol of a randomized controlled, double-blind, multicenter trial, aiming at evaluating the efficacy and safety of umbilical therapy for cirrhotic ascites, as a complementary and alternative therapy. Results of the current study will provide high-quality evidence supporting the management of ascites using umbilical therapy with TCM.

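### The only between-group test named for the continuous primary outcome is unadjusted, and level or change is left open; baseline-adjusted ANCOVA would be at least as efficient on either reading

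*Protocol article*

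**What the plan says.** Primary outcomes section: "The primary outcome measurement will be the depth of ascites". On timing: "It will be measured at baseline using B-ultrasound, after the intervention (10 days), and at the end of the 30-day follow-up period". The Discussion describes the same outcome differently, as "using the dynamic change of ascites by B-ultrasound as the primary outcome".

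Statistical analysis section, on comparing the groups: "To compare the difference between two groups, independent *t* tests (or the Mann–Whitney *U* test) will be used to analyze continuous data". On the repeated measurements: "Repeated-measures ANOVA will be used to account for the time effect". On the sites: "The data from all participating centers will be combined for statistical analysis". The Study design and setting section gives three centres. No baseline covariate and no centre term is named anywhere. Significance is judged two-sided at 0.05.

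**The concern.** Every patient contributes a baseline depth, and entry requires a depth above 3 cm with no upper limit across ascites grades 2 and 3, so patients may start from quite different depths. If baseline depth predicts later depth, a test that leaves it out carries variation that could have been removed.

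The named tests also fit several analyses: a t test on depth at follow-up, a t test on change from baseline, or a Mann–Whitney test on either. These can give different p values from the same data. The ANOVA does not settle the matter, because its stated purpose is time and the article does not say which of its terms would carry the treatment comparison.

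With a planned 82 patients and 78 already enrolled, a larger sample is hard to obtain. Precision from data already being collected is the cheapest available.

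**Working it through.** **The plan's own figure.** The Sample size section uses 87.5% against 62.5%, one-tailed α = 0.05, β = 0.20 and 10% dropout, giving 41 per group. The pooled two-proportion formula is

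n = [1.645·√(2·0.75·0.25) + 0.842·√(0.875·0.125 + 0.625·0.375)]² / 0.25² = 36.03, rounded up to 37.

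37 × 1.1 = 40.7, rounded up to 41. The figure reproduces, and 37 per group is the evaluable number used below. The calculation rests on proportions, so it gives no SD, mean difference or correlation for depth.

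**Assumptions for depth (none is in the documents).** A true difference d = 0.5 SD; the same SD σ at baseline and follow-up; correlation r between them from 0.3 to 0.8; 37 per arm; two-sided 0.05.

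**Variance of the quantity compared, per patient**
- Follow-up depth alone: σ²
- Change from baseline: 2σ²(1 − r)
- ANCOVA on baseline: σ²(1 − r²)

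The ratio of ANCOVA to follow-up only is 1 − r². The ratio of ANCOVA to change is (1 − r²)/[2(1 − r)] = (1 + r)/2. Neither exceeds 1, so ANCOVA is never the less precise of the pair, apart from one degree of freedom spent on the covariate.

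**Power.** The two-sample t test (noncentral t) was used, with the standardised effect equal to 0.5 divided by the square root of the variance in units of σ². For example, at r = 0.5 ANCOVA has 0.5/√0.75 = 0.577, and at r = 0.7 it has 0.5/√0.51 = 0.700.

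| r | ANCOVA variance ÷ follow-up only | ANCOVA variance ÷ change | Follow-up only | Change | ANCOVA |
|---|---|---|---|---|---|
| 0.3 | 0.91 | 0.65 | 56% | 43% | 60% |
| 0.5 | 0.75 | 0.75 | 56% | 56% | 69% |
| 0.7 | 0.51 | 0.85 | 56% | 78% | 84% |
| 0.8 | 0.36 | 0.90 | 56% | 92% | 94% |

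The difference detectable with 80% power at 37 per arm is 0.66 SD for follow-up only. For ANCOVA it is 0.66 × √0.75 = 0.57 SD at r = 0.5 and 0.66 × √0.51 = 0.47 SD at r = 0.7.

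**Level or change.** Write ANCOVA for the level as Y₁ = a + bT + cY₀. Subtracting Y₀ from both sides gives Y₁ − Y₀ = a + bT + (c − 1)Y₀. The treatment coefficient b and its standard error are unchanged, so the choice no longer affects the result.

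**Centre.** No between-centre variance is given and no stratification by centre is stated, so no gain from a centre term can be calculated.

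**The case against.** The strongest reply is that this is a condensed article. Covariate lists, centre terms and the rule for choosing Mann–Whitney are commonly left to an analysis plan that is not shown. That holds for detail, and none of those absences is counted here. But the article does state its between-group tests, and the point is that a better method exists than the one stated.

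It is also fair that an unadjusted comparison is valid under randomisation and that its standard error already allows for chance imbalance in baseline depth.

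A reader might infer several stronger things that the text does not support:
- *That baseline is ignored.* The article never says the tested variable is follow-up depth. The Discussion's wording points to change, and a test on change uses baseline. So would the group-by-time term of an ANOVA with baseline as one of its times.
- *That the power loss is large.* Against follow-up only at r = 0.3 the gain is about 4 points. Against change at r = 0.7 it is about 6 points (78% to 84%). Conventional treatment, including diuretics, is given to all patients, so r over the treatment period is unknown.
- *That the ANOVA dilutes the effect to two-thirds.* This requires baseline as a level and inference from the group main effect. The article states neither.
- *That patients with a missed visit are dropped, against intention-to-treat.* The Discontinuation section keeps the last recorded data in the analysis, and the Informed consent section retains data after withdrawal.
- *That pooling the centres costs power.* Combining data across sites does not rule out a centre term, and the effect cannot be computed.

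**Conclusion.** The point holds as one of efficiency and specification. The stated between-group test is unadjusted, the ANOVA is tied only to time, and the article points to depth in one section and to its change in another. ANCOVA on baseline depth is at least as efficient on both readings and removes the ambiguity.

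At d = 0.5 with 37 per arm, the gain over follow-up only runs from about 4 points (r = 0.3) to about 38 (r = 0.8: 56% to 94%). Over a change score it runs from about 17 points (r = 0.3: 43% to 60%) down to about 2 (r = 0.8: 92% to 94%). These figures rest on the assumed d and r and on equal SDs at the two times. The ordering of the methods does not depend on the value of r. There is no bias and the trial is not invalidated, but the change should be made.

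**What to change.** Before unblinding:

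1. Name one primary visit, and replace the t or Mann–Whitney test of the primary outcome by ANCOVA of depth at that visit on treatment and baseline depth, with centre as a further covariate. Report the adjusted mean difference in cm with its 95% CI.
2. If both follow-up visits are modelled, use a mixed model with baseline depth as covariate and treatment, visit, treatment-by-visit and centre as terms, and read the treatment contrast at each visit.
3. Keep Mann–Whitney as a sensitivity analysis.
4. Describe the outcome in the same terms in the Primary outcomes section and the Discussion.

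The cost is wording and an application to the Institutional Review Board, which the Ethics section requires for any protocol change. No new measurement is needed. The article states that the statisticians are blinded and that the trial is still enrolling, so the model can still be fixed without knowledge of the results.

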## Discussion

Umbilical therapy with TCM formulations has a long history in China, and has been popularly used to treat various diseases, including cirrhotic ascites. Through being applied to the umbilical region, TCM may be absorbed into the blood quickly and stimulate peripheral nerves, which may be the reason for its action. Also, as a complementary therapy, it is easy to operate and convenient, compared with acupuncture, moxibustion, and TCM soups.

Previous studies preliminarily showed that umbilical therapy is effective and safe in treating cirrhotic ascites [8, 9, 16–19]. One meta-analysis demonstrated that umbilical therapy was more effective in increasing 24-h urinary volume, decreasing patients’ weight and abdominal circumference, compared with conventional medicines. Adverse reactions were rarely reported, which often include skin itching or partial flushing due to the adhesive plaster [8]. Another meta-analysis of mirabilite umbilical compress in treatment of ascites in liver cirrhosis showed similar results [9]. Application of Shehuang Paste to the umbilical area was also reported to reduce blood flow of the portal vein and the splenic vein, and to lower the content of endotoxin, nitric oxide, and endothelin-1 [8].

However, the lack of high-quality evidences limits the application of umbilical therapy [8]. Most studies were small sample, unblind, and based on one medical center, which may lead to bias caused by confounding factors. Besides, some studies took the 24-h urinary volume, patients’ weight, and abdominal circumference change as primary outcomes, which could not reflect the dynamic change of ascites directly [18, 20]. Based on previous research [14], our study will be the first central-randomized, double-blind, parallel, placebo-controlled, multicenter trial, using the dynamic change of ascites by B-ultrasound as the primary outcome. In conclusion, we present the protocol of a randomized controlled, double-blind, multicenter trial, aiming at evaluating the efficacy and safety of umbilical therapy for cirrhotic ascites, as a complementary and alternative therapy. Results of the current study will provide high-quality evidence supporting the management of ascites using umbilical therapy with TCM.

## Trial status

The trial has been approved and registered. At the time of manuscript submission, the study has been actively enrolling subjects and, as of this writing, has a total of 78 subjects. The study is ongoing.

## Abbreviations

AE: Adverse event
ALT: Alanine aminotransferase
AST: Aspartate aminotransferase
CLDQ: Chronic Liver Disease Questionnaire
CONSORT: Consolidated Standards of Reporting Trials
CRF: Case report form
ECG: Electrocardiography
LSXG: *Lishui Xiaogu*
RCT: Randomized controlled trial
SAS: Statistical Analysis System
SPIRIT: Standard Protocol Items: Recommendations for Interventional Trials
TCM: Traditional Chinese medicine
GGT: Gamma-glutamyl transpeptidase
